#### Implementation

The KB strategy will be implemented and evaluated using an ITS. This approach is well-suited for assessing the effectiveness of population-level health interventions and testing their impact on specific outcomes within a defined impact model. We will conduct a multisite ITS study, accounting for the KB interventions in 5 different provinces. KBs who participated in previous Jooay studies will be invited to participate in a focus group to (1) review past KB practices, (2) rank strategies based on perceived effectiveness, (3) identify contextual factors influencing implementation, and (4) refine strategies for different settings. New KBs will be recruited and trained through interactive online workshops in purposefully selected provinces (British Columbia, Alberta, Saskatchewan, Ontario, Québec, and Yukon) and across sectors (families, youth, health, and education). KBs will identify new activities, update program information in their provinces, identify populations who may not know about the app, and develop strategies to disseminate within these provinces and promote the app to users (youth, families, clinicians, and educators) and community organizations within their scope of reach. Their insights will inform a 2-fold approach to innovation, sustainability, and use: (1) an automated system to optimize resource identification and updates within the Jooay database, and (2) an organic, human, and community-led dissemination process.

#### Effectiveness

We will evaluate the effectiveness of the app use on users’ engagement and participation in the community through two phases: (1) a nonrandomized mixed methods pilot feasibility study at the individual level and (2) an ITS study of the Jooay App implementation at the community level. Participants will include clinicians, parents of youth with disabilities of all ages, youth with disabilities aged 14 years and older, and educators. They will be recruited from the current user-base of the Jooay App (over 6000 users across Canada), through rehabilitation centers, community organizations, and schools that are part of the Jooay App research group, and social media and partner organizations’ mailing lists.

### Sample Size

This study includes three different sample-size considerations: (1) the ITS analysis of app engagement outcomes at the population level; (2) the recruitment of KBs to support the implementation of the app across Canadian provinces; and (3) qualitative interviews with KBs and feasibility study participants. Because these research components have different research objectives, the sample-size rationale differs across study components, as described below. For the ITS analysis, the primary unit of analysis will be the repeated time interval. ITS emphasizes the importance of repeated observations, underlying trends, and seasonal patterns when evaluating population-level interventions introduced at a clearly defined time point [24]. Therefore, engagement outcomes will be extracted from in-app analytics and aggregated monthly at the community level across all eligible app users. We will include a minimum of 12 monthly time points before and 12 monthly time points after the deployment of the gamified version of the Jooay App.

KBs will serve as provincial implementation partners who support raising awareness about the app across Canada. We will recruit at least 1 KB from each target province, for a minimum of 6 KBs, with the possibility of recruiting up to 2 per province where feasible. This will be determined during the preimplementation phase with current KBs and patient and community partners of the Jooay App research team. This approach will help us ensure sufficient representation across Canadian provinces, Jooay user types (eg, clinicians and parents), and communities with varying availability of adaptive and inclusive leisure activities. Qualitative interviews do not preclude a sample size. Purposeful, maximum variation sampling will be adopted to recruit KBs and feasibility study participants across sectors and regions of interest, with varied experiences and levels of engagement with leisure and their communities. We will also aim to recruit participants in regions where we know there is a limited offer of community-based activities to develop strategies that can support increased participation at the individual and community levels.

### Setting

#### Implementation

This study will be conducted in 5 provinces and 1 territory in Canada, with a focus on health care and community settings. A purposeful sampling strategy and a maximum variation sampling technique will be used to recruit KBs across provinces (British Columbia, Alberta, Saskatchewan, Ontario, Québec, and Yukon—these are the provinces where Jooay activities are most developed and previous KB strategies have been used), living in urban, suburban, and rural areas, and speaking French or English.

#### Effectiveness

For the pilot feasibility study of the mobile app, youth with different disabilities from different provinces and age groups (14‐29 y), parents, clinicians, and educators, living in urban, suburban, and rural areas, and speaking French or English will be recruited.

### Procedures

#### Implementation

KBs will be recruited across multiple Canadian provinces (British Columbia, Alberta, Saskatchewan, Ontario, Québec, and Yukon) and sectors (health, education, community organizations, families, and youth networks). Recruitment will follow a purposive and network-based strategy. Existing KBs and community partners involved in previous Jooay initiatives will first be invited to participate in an online focus group to review prior brokering strategies and identify contextually relevant approaches for scale-up. Additional KBs will be identified through professional networks, stakeholder recommendations, and community organizations (“natural” KB networks), including clinicians, educators, rehabilitation program managers, community leaders, and information hubs. Interested individuals will receive an email invitation outlining study objectives, procedures, and time commitment. Electronic informed consent will be obtained prior to participation. KBs will receive CAD $100 (CAD $1=US $0.72 as of March 1, 2026) per month for 6 months in recognition of their participation.

Prior to implementation, KBs will complete an online readiness-to-implement questionnaire informed by the capability, opportunity, motivation–behavior (COM-B) model [25]. The questionnaire will assess capability (knowledge of Jooay and inclusive leisure resources), opportunity (access to relevant professional and community networks), and motivation (intention and perceived importance of dissemination) [25]. Results will inform tailoring of training and support strategies. KBs will participate in monthly online meetings (Microsoft Teams) over 6 months. Meetings will include structured check-ins on dissemination activities, discussion of barriers and facilitators, and peer exchange of strategies across provinces. At the first meeting, KBs will determine preferred communication channels for ongoing exchange (eg, WhatsApp; Meta Platforms, Inc, or other group platforms). Meeting minutes and field notes will be documented for process evaluation. In the second meeting, we will provide a workshop on the new gamified version of the Jooay App. The latter meetings will be structured around the COM-B model based on the readiness to disseminate survey results. One meeting will focus on capability (knowledge of Jooay and inclusive leisure resources), another on opportunity (access to relevant professional and community networks), and one on motivation (intention and perceived importance of dissemination). KBs will be responsible for 3 main aspects. The first is identifying adaptive and inclusive leisure activities in their province. The second is sharing updated program information with the Jooay team. The third is disseminating the Jooay App to youth, families, clinicians, educators, and community organizations through existing networks. KBs will document dissemination activities using an online activity log. At the end of the 6-month implementation period, semistructured individual interviews will be conducted with KBs via Microsoft Teams. Interviews will explore dissemination experiences, perceived effectiveness of implementation strategies, contextual barriers and facilitators, and sustainability considerations. Interviews will be audio-recorded, transcribed verbatim, and anonymized. Process data will include monthly meeting notes, KB activity logs, and workshop evaluations. Qualitative data will be analyzed using thematic analysis. Deductive coding will be guided by the CFIR, with attention to intervention characteristics, inner setting, outer setting, characteristics of individuals, and implementation processes. The 2 researchers will independently code transcripts and resolve discrepancies through discussion. Descriptive statistics will summarize readiness-to-implement scores and dissemination indicators.

#### Effectiveness

After signing the consent, during the preparation phase for the pilot study, each participant will receive a tutorial guide for the Jooay App test version. This guide will include instructions on how to navigate and use the app’s various features. Following this, the primary author (EM) will meet individually with each participant, either in person or through an online video call, for an onboarding meeting. During this meeting, participants will be guided through the process of downloading and installing the app on their device, ensuring they feel comfortable with the setup and settings. Participants will have the opportunity to ask any initial questions or concerns regarding the app or study procedures. During the study period, participants will be encouraged to use the Jooay App regularly, engaging with its gamification features to support their participation in leisure activities and work toward their set goals. The research team will be available to answer questions, resolve technical issues, and provide additional guidance as needed. Participants will have direct access to the researcher via email and phone, allowing them to reach out at any time for assistance or clarification. Participants will agree on the periodicity and format of reminders they want to receive to use and engage with the app (eg, weekly, biweekly, monthly email reminders, text messages, or no reminders). The prompts and reminders will be registered in a participant’s “journal” for reference on the types of reminders that might contribute to higher or lower engagement. The preferred frequency and modes will be integrated into the broad public test version as in-app push notifications, email, or text reminders for users. At the end of the study, participants will complete an online survey on Microsoft Form (Multimedia Appendix 1) to capture their overall experiences and perceptions of the Jooay App, covering aspects such as user engagement, satisfaction with specific app features, and any perceived impact on their participation in leisure activities. Participants will be invited to individual semistructured interviews (Multimedia Appendix 2 for interview guide) via Teams to provide clarification and depth to their answers and experiences.

Following the completion of the pilot feasibility study, the gamified version of the app will be deployed to all users at the community level. The date of deployment of the gamified version will serve as the intervention point for an ITS analysis. This design was selected because gamification will be introduced at the app or community level and cannot be randomized across users once it is deployed. The ITS design will allow us to examine whether the introduction of the gamified version is associated with changes in the level and/or trend of engagement outcomes compared with patterns observed during use of the previous nongamified version. Engagement data will be extracted from in-app analytics and aggregated at monthly intervals. The preintervention segment will include monthly data from the previous nongamified version of Jooay, and the postintervention segment will include monthly data after deployment of the gamified version. We will include a minimum of 12 monthly time points before and 12 monthly time points after deployment to allow the estimation of baseline trends, postintervention changes, and seasonal patterns. Seasonality will be assessed through visual inspection of monthly trends. If seasonal patterns are identified, models will include calendar month indicators. We will also document other major app updates, holidays, school calendar periods, or external events that may influence engagement and consider these in adjusted or sensitivity analyses. Engagement outcomes will be measured using both backend and frontend indicators. Backend engagement measures will include app usage frequency, number of accesses, duration of use, and feature usage as captured through in-app analytics. Frontend engagement measures will include engagement with community-based features for youth users and the inclusion of community play and leisure activities within intervention plans developed by clinicians and educators. Additionally, following the deployment of the gamified version, participation in leisure will be assessed using newly co-designed in-app features that capture the number of activities users plan and attend, as well as users’ self-reported satisfaction and perceived achievement. These outcomes will be examined descriptively and longitudinally during the postintervention period to explore patterns of participation over time and their association with app engagement.

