### Objectives

The primary objective of this study is to evaluate whether the deployment of the gamified version of the Jooay App is associated with changes in app engagement compared with the previous nongamified version. Specifically, we will examine changes in app engagement following the deployment of the gamified Jooay App, using an interrupted time series (ITS) analysis of aggregated app analytics data.

The secondary effectiveness and feasibility objectives are to examine changes in specific engagement indicators, including app sessions, active users, duration of use, frequency of use, and use of key app features; to evaluate the feasibility of the gamified Jooay App among youth with disabilities, parents, and clinicians; and to explore postdeployment participation-related outcomes, including planned activities, attended activities, satisfaction, and perceived achievement.

The implementation objectives are to assess the process of implementing and scaling up the gamified Jooay App across participating Canadian provinces; to describe the expansion, role, and activities of the Jooay KB networks across these provinces; to identify provincial barriers and facilitators influencing app uptake, implementation, and sustainability; and to examine how the app and KB networks support the identification of community-based play and leisure opportunities for children and youth with disabilities.

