### Variables and Outcomes

#### Implementation

The implementation outcomes of this study include both process and intervention-related measures. The implementation process will be analyzed using the CFIR, focusing on outer setting, inner setting, and individual characteristics. The outer setting includes external influences such as patient needs, resources, and organizational networks. KBs recruited from each setting will undergo an initial assessment to identify key considerations, constraints to sustaining the KB role beyond the study, and an intake analysis of individual actions. These factors will be examined in initial KB analyses, monthly KB meetings, and a post hoc multisite analysis. Additionally, external factors such as cosmopolitanism (organizational networking), peer pressure, and policies or incentives supporting leisure-related outcomes will be assessed to determine their role in technology adoption and resource integration. The inner setting includes organizational characteristics affecting implementation, including team culture, intervention compatibility, goal-setting structures, leadership engagement, and implementation climate, which will be analyzed qualitatively through meeting minutes from monthly KB sessions. Individual characteristics, including KBs’ beliefs, knowledge, self-efficacy, and personal attributes influencing implementation, will be assessed during onboarding interviews with the research coordinator. User characteristics (eg, disability type, age, socioeconomic status, language, and technology familiarity) will be analyzed preimplementation during user-centered design activities and pilot testing. These insights will inform KBs’ strategies and interventions.

The implementation and intervention outcomes will assess the expansion of KB networks using social network analysis, as well as the growth in Jooay App users and their engagement levels. Additionally, partners with lived and living experiences (PWLEs) identified increased community awareness of leisure activities as a key implementation outcome, emphasizing its significance in post-COVID public policy and service restructuring. This outcome will be measured through quantitative indicators, including social network analysis and the number of new organizations and activities added to the app during the intervention period, compared with previous registration cycles.

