##### Community Level

Engagement will be measured using a segmented linear regression model to analyze changes over time, including preintervention trends, immediate changes before and after the intervention, and postintervention trends. Where appropriate, models will account for autocorrelation, seasonality, and nonindependence of repeated observations over time. App usage data will capture time spent and interactions with gamification features, with descriptive statistics assessing usage patterns by province, disability, and age among youth participants. Outcomes available only in the gamified version, including planned and attended activities, satisfaction, and perceived achievement, will be analyzed descriptively and longitudinally during the postintervention period rather than included in the primary ITS comparison.

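### The primary interrupted time series has no term for the study's own knowledge broker campaign, so the effects of gamification and promotion cannot be separated as planned

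*Protocol article*

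**What the plan says.** Objectives words the primary question thus: "evaluate whether the deployment of the gamified version of the Jooay App is associated with changes in app engagement compared with the previous nongamified version". Under Procedures, Effectiveness, the interruption is fixed: "The date of deployment of the gamified version will serve as the intervention point for an ITS analysis". Sample Size has engagement "aggregated monthly at the community level across all eligible app users", with "a minimum of 12 monthly time points before and 12 monthly time points after the deployment of the gamified version". The segmented linear model under Analysis, Community Level, has the usual terms, "including preintervention trends, immediate changes before and after the intervention, and postintervention trends", and accounts where appropriate for autocorrelation, seasonality and nonindependence.

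Procedures, Implementation, describes the KB programme. KBs are paid monthly for six months, and the third of their three duties is "disseminating the Jooay App to youth, families, clinicians, educators, and community organizations through existing networks". The programme is tied to the new version: "In the second meeting, we will provide a workshop on the new gamified version of the Jooay App". Variables and Outcomes, Implementation, counts among the KB outcomes the expansion of the networks, "as well as the growth in Jooay App users and their engagement levels".

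The KB strategy has its own multisite ITS (Sampling, Implementation; KB Intervention Evaluation), for which no start date or intervention point is given. Procedures, Effectiveness, lists other app updates, holidays, school periods and external events for adjusted or sensitivity analyses. It does not name KB activity. The limitations under Methodological Considerations do not mention the overlap.

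**The concern.** The study runs two of its own interventions on one outcome in one window, and the primary model carries a term for only one of them. A pooled total of clicks, logins or time in the app rises when KBs bring in users, whether or not gamification changes anyone's behaviour. The deployment coefficients absorb whatever part of that rise falls after release. A rise before release tilts the baseline trend against which the deployment is judged.

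The KB analysis has the mirror problem, since the release reaches every KB jurisdiction. A hybrid type II design is meant to answer both the effectiveness and the implementation question. As planned, neither analysis is protected from the other's intervention.

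**Working it through.** **Stated figure.** The plan gives a minimum of 12 + 12 = 24 monthly points and no power calculation, so there is no power figure to reproduce.

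**Calendar.** March 2026 to June 2027 is 16 months (Results). Twelve full post-release months ending in June 2027 require release by about 1 July 2026. Six KB months starting no earlier than March 2026 end no earlier than August 2026. July and August 2026 are therefore both KB and post-release months. If KB work starts at release, or later with its six months ending inside the window, all six KB months are post-release.

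**Bias model.** Inputs from the article are 12 pre and 12 post months, a six-month KB period, and the model terms (intercept, trend, level change, slope change). Assumed, because the article gives none of them: a true gamification effect of zero, a KB lift of size K, its shape, and its start relative to release. Least squares then fits a separate line to each 12-month segment. With months numbered x = 0 to 11, the mean is 5.5 and Sxx = 143.

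*KB start in the release month.* The pre line is zero. In the post segment the lift is K for x = 0 to 5:
- Sxy = (15 - 6 × 5.5)K = -18K, so slope = -18K/143 = -0.126K per month.
- Level = 0.5K + 5.5 × 0.126K = +1.19K.
- Mean post-release effect = 1.19K - 5.5 × 0.126K = +0.50K.
- The pre months contribute nothing, so a longer baseline leaves these values unchanged. For K = 20% the false level change is about 24%.

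*Start three months after release.* The lift covers x = 3 to 8, so Sxy = (33 - 33)K = 0, slope = 0 and level = +0.50K.

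*Gradual build-up from release (K/6, 2K/6, … K over six months).* The mean is 0.292K and Sxy = -7.58K. Slope = -0.053K and level = 0.292K + 5.5 × 0.053K = +0.58K.

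*Start four months before release.* The lift covers the last four pre months and the first two post months.
- The pre line has mean 0.333K and slope 16K/143 = 0.112K. It extrapolates to 0.333K + 6.5 × 0.112K = 1.06K at release.
- The post line has slope -10K/143 = -0.070K and starts at 0.167K + 5.5 × 0.070K = 0.55K.
- Level change = 0.55K - 1.06K = -0.51K. Slope change = -0.18K per month.

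| KB start relative to release (months) | Level bias (× K) | SE of level with KB term (SD) |
|---|---|---|
| -4 | -0.51 | 0.90 |
| -3 | -0.09 | 0.82 |
| -2 | +0.33 | 0.86 |
| -1 | +0.76 | 1.03 |
| 0 | +1.19 | 1.62 |
| +1 | +0.96 | 1.07 |
| +2 | +0.73 | 0.93 |
| +3 | +0.50 | 0.87 |
| +4 | +0.27 | 0.84 |
| +5 | +0.04 | 0.82 |

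Without a KB term the level SE is √(1/12 + 6.5²/143 + 1/12 + 5.5²/143) = 0.82 SD. Errors are taken as independent.

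**Longer baseline.** With 36 pre months, a start four months before release gives +0.14K instead of -0.51K.

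**False-positive rate.** These are 20,000 simulations per setting with a two-sided 5% t-test on 20 degrees of freedom. With a coincident start and no gamification effect, a positive level change is declared in 27% of series if K is 1 residual SD and in 75% if K is 2 SD, against a nominal 2.5%. With a start four months before release, a negative slope change is declared in 28% and 73%.

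**Lasting KB effect.** If KB work starts in the release month and its effect persists, the KB step equals the release step. The level bias is +1.00K, and no KB term in the pooled series can separate the two.

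**The case against.** The strongest reply is that KB effects are not ignored. They have their own province-level ITS and KBs keep an activity log. The phrase about external events could be stretched to cover KB work, and the objective claims only association. Dissemination is one of three KB duties. The lift, its shape and its start are all assumed here.

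Much of this stands, and it limits the point. A reader might infer that KB promotion will certainly be credited to gamification. The documents do not support that: no KB start or release date is given, the level bias can be negative, and it is near zero for a start five months after release. A reader might also infer that a geographic comparison is indispensable. It is not, because a KB term in the pooled series costs little precision once the starts differ by two or more months. Nor does the article provide ready controls. KB jurisdictions were chosen because Jooay is most developed there, and province appears in the Community Level analysis only for descriptive statistics among youth.

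The reply does not remove the core. The KB analysis is not linked to the deployment model and gives no KB intervention point. KB promotion is a planned study intervention, not an external event, and the text only undertakes to consider the events that it lists. This is also not a detail left to an analysis plan: the article itself fixes the interruption, the pooling, the model terms and the list of co-occurring events.

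**Conclusion.** The concern holds as a failure to separate two effects, not as a bias of known sign. As planned, a change in pooled engagement after release cannot be divided between gamification and KB promotion. If KB work starts at release or within about three months after it, the gamification level change is most likely inflated, by +0.50K to +1.19K for an immediate six-month lift and +0.58K for a gradual one starting at release. If it starts three to four months before release with only 12 pre months, the level bias is -0.09K to -0.51K.

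The overlap rests on two assumptions: that the 12 post-release months fit the stated data-collection window, and that KB work does not begin before March 2026. The size of K is unknown.

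**What to change.** 1. State the KB start and end dates by jurisdiction relative to the release date, and name KB activity among the co-occurring events under Procedures, Effectiveness.
2. Prespecify a KB-active term in the primary segmented model. Its cost is precision: the level SE goes from 0.82 to 1.62 SD if the starts coincide, and is about 0.82 to 0.93 SD if they differ by two or more months.
3. Use the province-level series that the multisite KB evaluation already requires, with non-KB jurisdictions as a supporting comparison where data allow. Confirm first that province is recorded for all users and for the pre-release months.
4. If the starts coincide or the KB effect lasts beyond the six months, word the primary conclusion as the joint effect of the gamified release plus KB promotion.
5. Report engagement per active user beside the totals as a secondary analysis. It should not replace the primary outcome: active users are themselves a listed engagement indicator, and newly recruited users change the make-up of the rate.

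The ITS and data analysis had not begun at submission, so this is a change of wording and model specification. The downside is a less precise level estimate.

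### With exactly 12 months before and 12 after deployment, adding calendar-month indicators leaves the level change and baseline trend inseparable, so the stated minimum does not suffice for the seasonally adjusted model

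*Protocol article*

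**What the plan says.** The Objectives section makes an interrupted time series of aggregated app analytics the primary analysis. Procedures, Effectiveness, says it will examine whether the gamified version is "associated with changes in the level and/or trend of engagement outcomes". The model in Analysis, Effectiveness, Community Level, is a segmented linear regression "including preintervention trends, immediate changes before and after the intervention, and postintervention trends", accounting for seasonality where appropriate.

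The series length is given twice. Sample Size says: "We will include a minimum of 12 monthly time points before and 12 monthly time points after the deployment of the gamified version". Procedures, Effectiveness, repeats the floor and adds what it is for: "12 monthly time points after deployment to allow the estimation of baseline trends, postintervention changes, and seasonal patterns". The same paragraph gives the seasonal rule: "Seasonality will be assessed through visual inspection of monthly trends", followed by "If seasonal patterns are identified, models will include calendar month indicators". Sample Size describes the data as one monthly community-level series: "engagement outcomes will be extracted from in-app analytics and aggregated monthly at the community level across all eligible app users".

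**The concern.** The article fixes three things together: a minimum series length, a form of seasonal adjustment, and a claim that the first is enough to estimate trend, change and season. With one year on each side, a full set of month effects uses up the information that would separate a steady rise across the two years from a jump at deployment. At the floor, the month effects and that separation cannot both be had.

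The level change is one of the two quantities that the protocol names for its primary objective. If season is seen and the stated remedy is applied to a series at the floor, software will typically drop a column or return one of infinitely many equivalent solutions. The printed immediate change then reflects that choice and not the app. Modelling autocorrelation does not help, because the defect is in the mean model.

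**Working it through.** **Inputs.** The series is 12 pre and 12 post months (Sample Size; Procedures, Effectiveness). The segmented model has an intercept, a baseline trend, a level change and a slope change (Community Level analysis). Season is entered as 11 calendar-month indicators (Procedures, Effectiveness). The article gives no power calculation or residual SD for this analysis, so there is no figure to reproduce. None is needed: whether a coefficient can be estimated depends only on the design matrix.

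**Step 1: the identity.** Let t = 1,…,24, let P = 1 from month 13 on, and let k = 1,…,12 be the position within each 12-month block. Then

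t = 12 × P + k.

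Each k corresponds to one calendar month, so k is a linear combination of the intercept and the 11 indicators. The time column is therefore an exact combination of columns already in the model. There are 4 + 11 = 15 columns and the rank is 14, which leaves 24 − 14 = 10 residual degrees of freedom. The rank is the same for all 12 possible release months.

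**Step 2: what can still be estimated.** Write β for the baseline trend per month, λ for the level change at the first post month and δ for the slope change. Subtract each pre month from the same calendar month a year later (j = 0,…,11):

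y(13 + j) − y(1 + j) = (λ + 12β) + δ × j + error.

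The month effects cancel. What remains identifies δ and the sum λ + 12β, but not λ or β alone.

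**Step 3: a numerical example.** A level change of +24 with no trend has λ + 12β = 24 + 12 × 0 = 24. A level change of 0 with a trend of +2 per month has 0 + 12 × 2 = 24. With the month effects shifted to match, the two give identical fitted values (largest difference about 3 × 10⁻¹⁴, which is rounding).

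**Step 4: pooling provinces.** Stacking five provinces with province intercepts and common month effects gives 19 columns and rank 18. The same dependence remains.

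**Step 5: when it resolves.** Standard errors of the level change are in residual SDs, from the diagonal of (X′X)⁻¹, assuming independent errors:

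| Pre + post months | Season term | Columns / rank | Residual df | SE of level change |
|---|---|---|---|---|
| 12 + 12 | none | 4 / 4 | 20 | 0.82 |
| 12 + 12 | month indicators | 15 / 14 | 10 | not estimable |
| 13 + 12 | month indicators | 15 / 15 | 10 | 1.41 |
| 12 + 13 | month indicators | 15 / 15 | 10 | 1.44 |
| 18 + 12 | month indicators | 15 / 15 | 15 | 0.92 |
| 24 + 12 | month indicators | 15 / 15 | 21 | 0.90 |
| 36 + 12 | month indicators | 15 / 15 | 33 | 0.75 |

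One extra month restores rank, but weakly: trend and level are then separated only through the single calendar month that occurs twice in the longer segment.

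**Step 6: would a sine-cosine pair rescue 12 + 12?** One annual pair gives 6 columns, rank 6 and an SE of 1.23 (0.81 at 18 + 12). It assumes a sinusoidal season, whereas the protocol itself names holidays and school calendar periods. As an assumed illustration, take a July–August bump of 10 units with no trend and no effect, at 12 + 12. The pair returns a false level change between −14.1 (September release) and +14.1 (July release). With no season term the range is −8.4 to +8.4.

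**The case against.** The strongest reply is that 12 is a floor and the indicators are conditional. Procedures, Effectiveness, allows more months. The pre-deployment data are existing analytics from an app developed in 2015 (Background and Rationale), and any extra month removes the exact dependence. Without indicators, 12 + 12 is full rank. This stands, and it confines the failure to one permitted branch of the plan. It does not rescue the sentence, which presents the floor itself as sufficient. Nor does anything commit the team to a longer series. Data collection is expected to end in June 2027 (Results), so 12 post months already require deployment by about the start of July 2026. That leaves little room on the post side.

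A second reply is that the objective is worded as level and/or trend, and the slope change survives. That is also correct.

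A reader might infer from the rank deficiency that the primary analysis is bound to fail, or bound to report a spurious jump. The documents support neither. Both conditions must hold before anything is lost, and then only two coefficients lose a unique value. What software prints depends on which column is dropped. If the time column goes, the printed level change is λ + 12β, which is correctly zero on average when there is neither trend nor effect, and which misleads only if read as a level change when a trend exists.

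**Conclusion.** The statement that 12 + 12 months allow baseline trend, postintervention change and seasonal patterns to be estimated is wrong when the protocol's own seasonal remedy is applied at exactly that minimum. In that case the level change and baseline trend are not separately estimable, while the slope change and λ + 12β are. This is algebra and rests on no assumed effect size or variance.

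The standard errors assume independent errors and a linear baseline. Autocorrelation would change those values but not the rank result. How many months of analytics were retained is not stated. The point matters because the affected quantity belongs to the primary objective, but it is a defect in one foreseeable branch of the plan and does not show that the whole interrupted time series is unsound.

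**What to change.** 1. In Procedures, Effectiveness, delete the statement that 12 + 12 months suffice for trend, change and season together, and align Sample Size with the new wording.
2. Where calendar-month indicators are used, require a pre-deployment series clearly longer than 12 months from existing analytics. Prefer 24 or more, so that each calendar month is seen at least twice before deployment. The gain in standard error from 18 to 24 pre months is small (0.92 to 0.90), so the reason for 24 is that coverage. Check first how many months were retained.
3. If no more than 12 pre months exist, report the slope change and the year-on-year contrast λ + 12β, and do not call the latter a level change.
4. Use a single sine-cosine pair only as a sensitivity analysis, and state its bias when season follows school terms or holidays.

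The cost is a wording change and a longer extract of existing data, with no new data collection. The price of the longer series is that a linear baseline is assumed over more months. The article reports that the interrupted time series has not yet begun, so the change can still be made before the data are analysed.
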